## Abstract

**Background:**

Impairments in upper limb motor function and cognitive ability are major health problems experienced by stroke patients, necessitating the development of novel and effective treatment options in stroke care. The aim of this study is to examine the effects of robot-assisted therapy on improving upper limb and cognitive functions in stroke patients.

**Methods:**

This will be a single-blinded, 2-arm, parallel design, randomized controlled trial which will include a sample size of 86 acute and subacute stroke patients to be recruited from a single clinical hospital in Shanghai, China. Upon qualifying the study eligibility, participants will be randomly assigned to receive either robot-assisted therapy or conventional therapy with both interventions being conducted over a 6-week period in a clinical rehabilitation setting. In addition to comprehensive rehabilitation, the robot-assisted therapy group will receive a 30-min Armguider robot-assisted therapy intervention 5 days a week. Primary efficacy outcomes will include Fugl-Meyer Assessment for Upper Extremity (FMA-UE) and Mini-Mental Status Examination (MMSE). Other secondary outcomes will include Trail Making Test (TMT), Auditory Verbal Learning Test (AVLT), Digit Symbol Substitution Test (DSST), and Rey–Osterrieth Complex Figure Test (ROCFT). All trial outcomes will be assessed at baseline and at 6-week follow-up. Intention-to-treat analyses will be performed to examine changes from baseline in the outcomes. Adverse events will be monitored throughout the trial period.

**Discussion:**

This will be the first randomized controlled trial aimed at examining the effects of robot-assisted therapy on upper limb and cognitive functions in acute and subacute stroke patients. Findings from the study will contribute to our understanding of using a novel robotic rehabilitation approach to stroke care and rehabilitation.

**Trial registration:**

Chinese Clinical Trial Registry ChiCTR2100050856. Registered on 5 September 2021.

## Background

Stroke is the second leading cause of death and the third leading cause of disability globally [1, 2]. In China, there are approximately 3 million new stroke cases diagnosed annually which impose an enormous burden on family, society, and healthcare systems [3–5]. Motor and cognitive dysfunction are common complications among stroke patients following stroke and they often coexist [6]. Approximately 65% of post-stroke patients live with upper limb dysfunction [3] and up to 75% exhibit cognitive impairment [7–9]. The prevalence of concurrent impairment ranges from 10 to 23% [10]. Previous studies have shown that motor performance is associated with global cognition, memory, and executive function and that cognitive dysfunction may attenuate post-stroke mobility recovery [10–12]. Upper limb and cognitive dysfunction have also been shown to significantly affect the quality of life, functional recovery process, and social participation among patients after stroke [7, 13–15]. Therefore, efforts to identify effective post-stroke rehabilitation treatments aimed at improving upper limb and cognitive functions are of high clinical importance for stroke care.

There is currently a lack of high-quality evidence or clinical practice guidelines supporting the use of any specific intervention as a part of routine practice. Conventional rehabilitation approaches (e.g., manual therapy techniques, task-specific training, mental practice, and sensory intervention) [16] require patients to perform partial or full movements with both assistance and supervision of a therapist. Such interventions have been shown to be both time-consuming and labor-intensive in clinical rehabilitation settings [17].

Robot-assisted therapy is a novel approach for the provision of a safe, repetitive, intensive, and quantitative rehabilitation intervention [18]. Since its initial deployment in clinical research [19], there has been an increasing number of studies that have reported its potential in facilitating recovery of upper limb and cognitive functions [20–23]. A recent review concludes that robot-assisted training can significantly improve upper limb motor impairment among stroke patients [20]. However, other studies have indicated that robot-assisted training may not be clinically superior to usual care in helping improve functional outcomes after stroke [21, 22]. In addition, previous research has mainly focused on assessing the effects of robot-assisted training on motor performance and recovery, its effectiveness on improving cognitive function has not been fully investigated. A previous pilot study reported improved cognitive outcomes after robot-assisted training in patients with stroke. However, the lack of a control group has made it impossible to draw meaningful clinical conclusions from the study [23]. Therefore, in the current study, we aim to conduct a comparative study examining the efficacy of a robot-assisted therapy, compared with a conventional treatment therapy in improving upper limb and cognitive functions among acute and subacute stroke patients.

## Methods

### Objectives

The objectives of the study are:To evaluate the effects of robot-assisted therapy on improving upper limb function in acute and subacute stroke patientsTo test the effectiveness of robot-assisted therapy on improving cognition in acute and subacute stroke patients

### Trial design

This study will involve a single-blinded, 2-arm, parallel design, randomized controlled trial with a 1:1 allocation ratio. Eligible patients will be randomly assigned to a robot-assisted therapy group or a conventional therapy group and receive their respective intervention treatment for 6 weeks. The study protocol is presented following the SPIRIT reporting guidelines [24], which is shown in Fig. 1.

**Fig. 1 Fig1:**
[figure not shown]
SPIRIT flow chart RCT study of patients with stroke

### Recruitment and participants

Study participants will be recruited from the First Rehabilitation Hospital of Shanghai, China. Recruitment strategies will include posting research advertisements to the patients or their caregivers at multiples site in the hospital. Other recruitment methods include the use of word of mouth and social media. Interested patients or caregivers will be encouraged to contact research staff via telephone.

Patients will be included if they (1) are aged 18–65 years; (2) diagnosed with stroke by computed tomography or magnetic resonance imaging within 6 months following stroke onset [25]; (3) have a unilateral stroke for the first time; (4) have cognitive impairment (as determined via a Montreal Cognitive Assessment [MoCA] cut-off score of 26) [26, 27]; and (5) have severe upper limb functional deficits (Fugl-Meyer Assessment for Upper Extremity [FMA-UE]. 0–28) [23].

The exclusion criteria comprise the following: (1) severe visual, auditory, or speech impairments; (2) a history of epilepsy or serious heart, lung, liver, or kidney disease; (3) participation in robot-assisted training or other intervention programs in the past 3 months; and (4) inability to complete the entire intervention as required.

Participants will be considered withdrawal from the study if they (1) make a request to withdraw from the study; (2) show any serious adverse reactions to the robot-assisted therapy treatment; or (3) develop a serious disease that preclude them from continuing treatment.

### Procedure

The trial will be conducted in an academic setting located in a research laboratory. At an initial visit, patients and their caregivers will be provided with an introduction of the study protocol, which will include the detail about study procedures, intervention conditions, group randomization, and outcome assessments. All patients will provide written informed consent prior to participation in the study. Participants’ demographic and clinical characteristics, as well as the study outcomes, will be assessed at baseline. All outcome measures ascertained at baseline will be repeated at 6-week follow-up. The study protocol has been approved by the ethics committee of the First Rehabilitation Hospital of Shanghai. The schedule of enrollment, assessments, and interventions is shown in Fig. 2.

**Fig. 2 Fig2:**
[figure not shown]
Schedule of enrollment, assessments, and interventions. The × symbol indicates the specific time point at which the corresponding measurement will be taken

### Randomization and blinding

#### Sequence generation

Upon completion of baseline measurements, qualified patients will then be randomly assigned to one of the intervention groups. A computer-generated randomization sequence, generated by a statistician, will be used.

#### Interventions

All patients will receive comprehensive rehabilitation therapy (45 min a day, 5 days a week over 6 weeks) that includes one-to-one physiotherapy and occupational therapy delivered by a certified physical and occupational therapist, respectively. In addition to the comprehensive therapy, the robot-assisted therapy group will receive physical training using the Armguider upper-limb robotic (ZD MEDTECH, Shanghai, China), which is an intelligent rehabilitation training system specially designed for people with upper limb or cognitive dysfunction. The system can provide passive, assistive, and active planar movements around the shoulder, elbow, and wrist joints. During treatment, participants will be asked to perform both motor and cognitive tasks shown in a game scene that generates real-time auditory and visual feedback. The planned games to be implemented in the study are described below (see also Fig. 3).Butterfly Capturing: Patients will be asked to control the net to capture a flying butterfly moving in different directions (this aims to assess visual-spatial ability and executive function)Playing Cards: A series of cards will be shown and then turned over. The patients will be asked to point out the cards with the same pattern (this aims to assess attention, scanning, memory, and delayed recall)Calculation: Patients will be asked to calculate the equations and move the correct answer to the designated position (this aims to assess computing ability)Fruit Ninja: Patients will be asked to observe the fruits that appear on the screen and cut them into sections while avoiding hitting obstacles (this aims to assess attention, graphic processing ability, response ability, and processing speed)Supermarket Shopping: Patients will be asked to buy the items on the list and pay the correct value of currency (this aims to assess visual scanning, selective attention, divided attention)Little Bird Flying: Patients will be asked to control a bird passing through pillars of different heights and avoid hitting obstacles (this aims to assess visual scanning and judgment ability)

**Fig. 3 Fig3:**
[figure not shown]
During treatment, patients will be asked to perform both motor and cognitive tasks shown in a game scene that generates real-time auditory and visual feedback. **A** Butterfly Capturing. **B** Playing Cards. **C** Calculation. **D** Fruit Ninja. **E** Supermarket Shopping. **F** Little Bird Flying

Participants will spend 5 min on playing each of the six games described previously. When a game is completed, the system automatically and randomly switches to another game. The difficulty level of each game will be adjusted individually based on the patient’s ability and improvement. The intervention with the Armguider robot-assisted therapy will last 6 weeks, implemented at 30-min a day for 5 days a week. Patients will be monitored by research staff during the intervention period for potential adverse events including physical and/or emotional responses to games.

#### Primary outcomes

##### Fugl-Meyer Assessment for Upper Extremity

The FMA-UE assesses upper limb impairment and consists of 33 items. Performance is scored on a three-point ordinal scale (0, 1, or 2), with a maximum score of 66 points. The items are summed to provide a final score; a higher score indicates minimal or no impairment [28, 29].

##### Mini-Mental Status Examination (MMSE)

Global cognitive function will be assessed using the MMSE scale. MMSE is a single-page, 30-point test, which requires approximately 10 min to complete. It assesses different cognitive domains, including visuospatial/executive, naming, memory, attention, language, abstraction, delayed recall, and orientation; a higher score indicates better global cognitive function [30].

#### Secondary outcomes

##### Trail Making Test

Executive abilities will be evaluated through the TMT. The TMT includes parts A and B. In part A, patients are given a sheet of paper with circled numbers (from 1 to 25) and asked to draw lines to connect the numbers in ascending order, as quickly and accurately as possible. In part B, patients are again asked to connect the circles in ascending order, but are also instructed to alternate between numbers and letters. The time in seconds to complete each task is then analyzed [31, 32].

##### Auditory Verbal Learning Test

Memory will be measured using the AVLT. The assessor reads 12 two-character words randomly, and then the patients are required to recall the words. The test scores are calculated as follows: (1) AVLT Immediate Recall (AVLT-IR): the total of the correct recall words in the first three trials; (2) AVLT Short-term Delayed Recall (AVLT-SR): the sum of correct responses of free recall after short-term delayed (approximately 5 min); (3) AVLT Long-term Delayed Recall (AVLT-LR): the sum of correct responses of free recall after long-term delayed (approximately 20 min); (4) AVLT Category-cued Recall (AVLT-CR): the total of the correct answers under the category-cued recall condition; and (5) AVLT Recognition Test (AVLT-REC): the total of the correct answers in the recognition test [33].

##### Digit Symbol Substitution Test

Attention and processing speed will be assessed with the DSST. In this test, patients are given a sheet of paper with nine symbols and corresponding numbers from 1 to 9. Patients are instructed to write down each symbol under its corresponding number within 90 s; the number of correct answers are then scored [34].

##### Rey–Osterrieth Complex Figure Test

Visuospatial abilities and visual memory will be evaluated using the ROCFT. In this assessment, patients are asked to complete a complicated geometrical figure, which is comprised of 18 elements. Each element is scored on a two-point scale (0, 1, or 2) based on accuracy and placement, with a higher score indicating a better performance [35].

#### Other measures

These will include baseline demographic measures that assesse patient demographic characteristics (e.g., age, sex, stroke type [hemorrhagic/ischemic], educational level, affected side, time after stroke, handedness). In addition, history of disease will also be collected with a self-reported questionnaire.

### Statistical methods

#### Sample size and power

The sample size in this study is based on the expected difference between the two intervention groups in the outcome measure of FMA-UE score. We based our intervention effect from the existing literature on the effects of robotic training involving patients with stroke. With a predicted medium size effect, our power calculation indicated that, with a sample size of 78 stroke patients, we will have statistical power of 80% (at a two-tailed significance level of 0.05) to detect a between-group mean difference at an effect size of 0.65 for FMA-UE [36]. Power calculations were performed using G_*_Power free software (Version 3.1.9.4). Assuming a 10% attrition rate, we plan to enroll a total of 86 patients.

### Statistical methods for primary and secondary outcomes

With intention-to-treat, participants will be analyzed according to their assigned randomization group regardless of their participation status. Descriptive statistics will be performed to describe study population and patients’ demographical and clinical characteristics at baseline. Continuous variables and categorical variables will be presented as mean ± standard deviation or percentages, respectively. Baseline demographic descriptors will be compared across groups, using analysis of variance for continuous variables and the chi-square (or Fisher’s Exact) test for categorical variables.

For primary and secondary outcome analyses, we will use repeated measures analysis of variance (ANOVA) to compare pre- and post-intervention changes at 6-week follow-up in the repeated outcome measures (a within subject factor) between the two intervention groups (a between group factor). Analyses will be conducted with and without important adjustments for baseline covariates (e.g., age, gender, stroke type, affected side) using either ANOVA or analysis of covariance (ANCOVA) statistical models. Pre- and post-intervention change scores on the primary and secondary outcome variables and their 95 percent confidence intervals will be computed to determine the intervention effects. Two-sided *P* values of less than 0.05 will be considered to indicate statistical significance. No subgroup or supplemental analyses are planned. All statistical analyses will be performed using SPSS version 25 (IBM Corp., Armonk, NY, USA), with the significance level set at *p* ≤ 0.05.

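### The intention-to-treat promise conflicts with a rule that withdraws patients from the study and a model that needs both scores, so unless withdrawn patients are still assessed the result is a completers analysis

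*Protocol article*

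**What the plan says.** Four statements in the protocol article bear on this point.

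- **Analysis principle** (Statistical methods for primary and secondary outcomes): under intention-to-treat, "participants will be analyzed according to their assigned randomization group regardless of their participation status". The Abstract also announces intention-to-treat analyses of change from baseline.
- **Withdrawal** (Recruitment and participants): "Participants will be considered withdrawal from the study if they (1) make a request to withdraw from the study", or (2) "show any serious adverse reactions to the robot-assisted therapy treatment", or (3) "develop a serious disease that preclude them from continuing treatment". The rule is worded as leaving the study. It does not separate stopping therapy from ending assessment.
- **Assessment and model**: the Procedure section repeats the baseline measures once, at 6 weeks. For the primary and secondary outcomes, "we will use repeated measures analysis of variance (ANOVA) to compare pre- and post-intervention changes at 6-week follow-up", with time within subjects and group between subjects. Change scores with 95% confidence intervals give the effect.
- **Expected loss and further analyses**: "Assuming a 10% attrition rate", the Sample size and power section goes from 78 patients to 86. The statistical methods section closes the other route: "No subgroup or supplemental analyses are planned".

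**The concern.** The stated rules do not fit together. A patient who leaves the study before week 6 has no post-baseline score, and the named model cannot use a patient without one. If the withdrawal rule and the model are followed as written, the patients analysed are those who stayed. That is not an analysis regardless of participation.

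One of the three withdrawal grounds can be met only by patients allocated to the robot. If the patients removed on that ground would have had different outcomes from the rest of their arm, the two groups compared are no longer the randomised groups, yet the report would still call the result intention-to-treat. As worded, the plan also excludes the sensitivity analysis that would show whether this matters.

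**Working it through.** **1. The plan's own figures.** Two-sample t-test, effect size 0.65, two-sided 0.05, power 80%: the noncentral t solution is 38.14 per arm, so 39 per arm and 78 in total (power 80.9%). The plan's 78 reproduces. For attrition, 78 × 1.10 = 85.8, which rounds to the plan's 86; dividing instead gives 78 / 0.90 = 86.7, so 87. The difference is immaterial. With 86 enrolled, 86 × 0.90 = 77.4 patients are expected to complete. The power calculation therefore already rests on completers and expects about 8 or 9 losses. With 8 lost, completer power at 0.65 is 80.5–80.9% however the loss is split between arms. The issue is bias, not power.

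**2. What the model uses.** Let D be the 6-week score minus the baseline score. With two time points, the group-by-time F statistic equals the square of the two-sample t statistic on D. A patient without a 6-week score has no D and contributes nothing. ANCOVA of the 6-week score or of D has the same limit.

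**3. How large the bias could be.** The documents do not give the number lost by arm or the outcomes of those lost, so both are assumed. Take 43 per arm, no true effect, and loss only in the robot arm. Let m patients be lost, who would have scored on average k SD below their arm's mean. With f = m/43, the completers' mean is too high by

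bias = f·k / (1 − f) = m·k / (43 − m).

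The type I error is the two-sided rejection probability of the noncentral t with noncentrality bias / √(1/(43 − m) + 1/43) and 84 − m degrees of freedom. For m = 4, k = 1: bias = 4/39 = 0.103 SD, standard error √(1/39 + 1/43) = 0.221, noncentrality 0.464, 80 degrees of freedom, rejection 7.4%.

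| Lost, robot arm only | Bias, k = 0.5 to 1 (SD) | Share of 0.65 | Type I error |
|---|---|---|---|
| 1 | 0.01 to 0.02 | 2 to 4% | 5.0 to 5.1% |
| 2 | 0.02 to 0.05 | 4 to 8% | 5.1 to 5.6% |
| 4 | 0.05 to 0.10 | 8 to 16% | 5.6 to 7.4% |
| 8 | 0.11 to 0.23 | 18 to 35% | 7.9 to 16.8% |

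With k = 0 there is no bias for any m, and with k negative the sign reverses. The last row puts nearly all the planned attrition in one arm, so it is an upper-end case.

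**4. Simulated loss.** These runs have the same setting, with 4 of 43 (about 10%) lost according to a variable correlated with the outcome. A correlation of 0.3 gives +0.05 SD and 5.8%; 0.5 gives +0.09 SD and about 7%. Removing exactly the 4 worst gives about 0.17–0.18 SD (27% of 0.65) and 14–15%. With 2 lost, correlations of 0.3 and 0.5 give +0.03 and +0.05 SD, and a type I error of 5.1–5.6%.

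**The case against.** The strongest reply is that nothing in the article says withdrawn patients go unassessed or are deleted. The Procedure section has all measures repeated at 6 weeks, and imputation before the ANOVA would be compatible with the intention-to-treat sentence. Such detail is often left to the full protocol or SAP, which are not shown. This stands in part: silence on a missing-data method is not the finding, and a completers analysis is conditional on withdrawal ending assessment. What remains is a conflict between stated rules. Withdrawal is worded as leaving the study, the named model needs both scores, and supplemental analyses are excluded.

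It is also fair to say that the arm-specific ground may rarely be met. The adverse event section states that the literature reports no serious or major harms from robotic rehabilitation in stroke, and the other two grounds apply to both arms. This stands, and is why the mild rows of the table matter as much as the severe ones.

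Three stronger readings are tempting, and none is supported.

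- A reader might take the exclusion for "inability to complete the entire intervention as required" as a way to remove randomised patients. It is listed among the exclusion criteria, apart from the withdrawal list. The sections on sequence generation and allocation concealment have staff apply those criteria to decide eligibility, and only qualified patients are randomised. It is a screening judgement.
- A reader might infer that poor responders are withdrawn and the robot arm is thereby favoured. No withdrawal ground refers to response, so the documents do not give the direction of bias.
- A reader might infer that replacing the ANOVA with a mixed model would solve the problem. With one follow-up visit, such a model recovers little. With 4 robot patients lost, a loss correlation of 0.5 and a baseline correlated 0.5–0.85 with the 6-week score, bias falls only from 0.09 to 0.07–0.09 SD when loss depends on change. When loss depends on the 6-week score, it rises from 0.02–0.04 to 0.04–0.07 SD.

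**Conclusion.** The point holds as a conflict between the intention-to-treat statement, the withdrawal rule and the named model. Unless withdrawn patients are still assessed at 6 weeks, the stated plan yields a completers analysis labelled intention-to-treat, and one of its three removal grounds is specific to the robot arm.

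The possible harm runs from negligible, with one or two losses, to modest with four: up to about 0.10 SD, and a type I error near 7%, when lost patients would have done up to 1 SD worse. The 14–15% figure needs exactly the worst tenth of the robot arm to be lost and no loss among controls. All these sizes rest on assumed numbers, an assumed outcome gap and one-sided loss. The sample size is not called into question.

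The point is still worth acting on now. The trial is recruiting, and a 6-week score that was not taken cannot be recovered later.

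**What to change.** Leave the clinical stopping reasons as they are and reconcile the two sections:

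1. In Recruitment and participants, define the listed events as discontinuing study therapy, not leaving the study. For a patient's own request, record separately whether consent to follow-up is also withdrawn.
2. Collect the 6-week outcomes on every randomised patient unless consent to follow-up is withdrawn. This step does most to limit the bias.
3. In the statistical methods section, or the SAP, state how randomised patients who still lack a 6-week score enter the intention-to-treat analysis.
4. Replace the sentence excluding supplemental analyses with one that provides for a single missing-data sensitivity analysis, delta-adjusted by arm, showing how much worse the unobserved robot-arm outcomes would have to be to change the conclusion.

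The cost is the rewording, 6-week assessments of some patients who have stopped therapy, and one extra analysis. About 8 or 9 losses are planned for in total, so the added visits should be few.

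### The two-time-point repeated measures ANOVA is a valid change-score test, but ANCOVA on each outcome's own baseline would be at least as precise at no cost and should be the named primary model

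*Protocol article*

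**What the plan says.** Under *Statistical methods for primary and secondary outcomes*, the protocol article sets the model: "we will use repeated measures analysis of variance (ANOVA) to compare pre- and post-intervention changes at 6-week follow-up in the repeated outcome measures", with group as the between-subject factor. Change scores with 95% confidence intervals are to serve as the measure of the intervention effect. Analyses are to be run with and without "important adjustments for baseline covariates (e.g., age, gender, stroke type, affected side"), by either ANOVA or ANCOVA. The outcome's own baseline value is not in that list, and the article does not say which of these analyses is primary.

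The *Procedure* section gives only two assessments, baseline and 6 weeks. *Sequence generation* places the baseline measurements before randomisation.

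Under *Sample size and power*, the trial is sized "to detect a between-group mean difference at an effect size of 0.65 for FMA-UE", "at a two-tailed significance level of 0.05", "with a sample size of 78 stroke patients". The section gives neither a baseline-to-follow-up correlation nor the SD on which 0.65 is standardised.

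**The concern.** With two time points, the group-by-time term of a repeated measures ANOVA is algebraically the two-sample t-test on change. That test subtracts the whole baseline value, whereas ANCOVA subtracts only the part that predicts the follow-up value. The baseline of the outcome is usually the most useful covariate, and here it will already have been recorded before allocation.

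Three things are at stake:
- precision of the treatment effect for every outcome;
- whether the planned test keeps the stated power for FMA-UE;
- how far a chance baseline difference between two arms of about 43 moves the estimate.

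**Working it through.** **Inputs from the article.** Two-sided alpha 0.05; power 80%; effect size 0.65; 78 evaluable patients, which is 39 per arm under 1:1 allocation (*Trial design*); 86 enrolled.

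**Assumptions, not in the article.** rho is the within-arm correlation of baseline and 6-week values. k is the baseline SD divided by the 6-week SD. Ranges are shown for both.

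**Step 1: the article's own figure.** For a two-sample t-test with n per arm, the noncentrality is d × sqrt(n/2) = 0.65 × sqrt(39/2) = 2.87 on 76 degrees of freedom. Power is 0.809 at 39 per arm and 0.799 at 38, so 78 is the smallest balanced total that reaches 80%. Adding 10% gives 78 × 1.10 = 85.8, hence 86. The plan's figures reproduce.

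**Step 2: variances, in units of the 6-week variance.**
- Change score: 1 + k² − 2·rho·k, which is 2(1 − rho) when k = 1.
- ANCOVA on the same outcome's baseline: 1 − rho².
- Difference: (k − rho)², which is never negative and is zero only when rho = k.

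Variance of change relative to ANCOVA:
- k = 1, rho 0.3: 1.40/0.91 = 1.54
- k = 1, rho 0.5: 1.00/0.75 = 1.33
- k = 0.7, rho 0.3: 1.07/0.91 = 1.18
- k = 0.7, rho 0.5: 0.79/0.75 = 1.05

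**Step 3: power at 39 per arm if 0.65 is on the 6-week SD.** The effective standardised difference is 0.65 divided by the square root of the variance above (75 degrees of freedom for ANCOVA).

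| rho | change, k = 1 | change, k = 0.7 | change, k = 0.5 | ANCOVA |
|---|---|---|---|---|
| 0.3 | 0.668 | 0.782 | 0.828 | 0.844 |
| 0.5 | 0.809 | 0.890 | 0.905 | 0.905 |
| 0.7 | 0.955 | 0.978 | 0.969 | 0.978 |

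Simulation with k = 1 agrees. Change against ANCOVA was 0.671 and 0.851 at rho 0.3, 0.811 and 0.903 at rho 0.5, and 0.957 and 0.976 at rho 0.7.

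The change test matches the plain t-test on the 6-week value when 1 + k² − 2·rho·k = 1, that is, at rho = k/2. The 80% line lies just under that, at about 0.49 when k = 1. At k = 0.6 and rho = 0.3, exactly at break-even, change power is 0.809.

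**Step 4: power if 0.65 is on the change SD.** The planned test then keeps 0.809 whatever rho is. With k = 1, ANCOVA has effective difference 0.65/sqrt((1 + rho)/2) and power 0.955, 0.905 and 0.867 at rho 0.2, 0.5 and 0.7.

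**Step 5: chance imbalance.** With 43 per arm, the 95% limit for a baseline difference is 1.96 × sqrt(2/43) = 0.42 baseline SD. Given such a difference, the expected change contrast moves by (k − rho) × 0.42 follow-up SD. This is 0.21 at k = 1 and rho 0.5, 0.13 at k = 1 and rho 0.7, and 0.08 at k = 0.7 and rho 0.5.

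**The case against.** Four stronger conclusions might be inferred, and the article does not support them.

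**That the trial is underpowered.** This needs 0.65 to be standardised on the 6-week score and rho to be low, and neither is stated. A two-sample calculation fits an effect size on change scores equally well, and the article does take change scores as its effect measure. The entry limit of FMA-UE 0–28 might be offered as a reason for a low correlation on a 66-point scale. The same limit also shrinks the baseline SD, which lowers the break-even correlation and much of the loss: at rho 0.3, change power rises from 0.668 at k = 1 to 0.828 at k = 0.5. The equal-SD figures are therefore not a safe default for this outcome.

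**That the estimate is biased.** Over randomisations the change-score contrast is unbiased and its type I error is controlled. The shift in Step 5 is conditional on the imbalance observed, and 0.42 SD is a 95% limit rather than a typical case.

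**That baseline adjustment is ruled out.** The covariate list is given by example and ANCOVA is mentioned, so the outcome's baseline is unnamed, not excluded. A condensed article may also leave the full covariate list to another document.

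**That the sample size is wrong.** It reproduces.

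These objections stand. They do not remove the point, because the article does more than omit a detail: it names a change-based model and a change-based effect measure. In that model the baseline is already one of the two responses, so an open covariate list does not naturally bring it in.

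**Conclusion.** The planned analysis is valid, but it is at best as efficient as ANCOVA on the outcome's own baseline (apart from one degree of freedom) and is less efficient unless rho = k. Over rho 0.3 to 0.5, the excess variance is 54% to 33% with equal SDs and 18% to 5% if the baseline SD is 0.7 of the follow-up SD. The direction needs no assumed value of rho or k; the size depends on both.

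A fall below 80% power is possible but not shown. It requires 0.65 on the follow-up SD and rho below about k/2. If 0.65 is on the change SD, planned power is 0.809 and the plan only forgoes extra power. This is a free improvement and a recommendation, not an error that invalidates the trial.

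**What to change.** Name ANCOVA as the primary analysis for each outcome: the 6-week value as response, treatment group as factor, and the same outcome's baseline value as covariate. Report the adjusted between-group difference with its 95% confidence interval. Keep the sample size. In the sample size section, state whether 0.65 refers to the SD of the 6-week score or of the change. At 39 per arm, ANCOVA power was at least 0.809 under both readings at every correlation computed (0 to 0.9; equal SDs for the change-SD reading).

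The cost is one sentence in the analysis section and a clause in the sample size section. No extra patients, visits or data are needed, and the planned software fits the model. Recruitment is under way, so the change should be recorded before outcome data are seen by group.
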